### Data analyses

#### Qualitative analysis

On a quarterly basis, we will analyze data from each clinic site using a comparative case analysis [63]. Organizational level data and interview transcripts will be organized, read and coded in ATLAS.ti. Data will be analyzed on an ongoing basis, and a working summary of emergent findings will be updated as incoming data is added. As a validity check of qualitative results, we will check relevant data interpretations against all new data using a constant comparison approach [64]. We will note similarities and differences of implementation feasibility between practice sites based on clinic characteristics and from data provided in interviews. Each quarter all quantitative and qualitative results will be summarized in brief reports to be shared with the research team for reflections on any changes needed. These analyses represent ongoing monitoring and feedback to inform refinements of the implementation strategy and clinical trial procedures to refine implementation strategy to better fit local needs and contexts.

### Quantitative analysis

Descriptive statistics will be used to summarize patient and clinic characteristics. We will declare our intervention a success if at least 25% of those unscreened are screened at 12-month follow-up in this difficult to reach population. We will declare the optimization of screening a success if 15% of those unscreened are screened with a colonoscopy or flexible sigmoidoscopy at 12-months. Overall improvement metrics are comparable to improvements in previous CRC screening implementation studies in FQHCs [65, 66]. At baseline, we will calculate average screening rates and their confidence intervals across all practice sites in intent to treat analyses and at 12-months we will assess screening rates and their confidence intervals for all sites. The confidence intervals will be compared to 25%. We will compare differences in CRC screening by glucose control, sex, and race/ethnicity.

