Guided by the insights of the exploration and preparation phases, we developed the Strategic Use of Resources for Enhanced ColoRectal Cancer Screening in Patients with Diabetes (SURE: CRC4D) implementation toolkit, which includes tailorable materials and protocols that will be tested in a single arm, hybrid type 2 effectiveness-implementation single arm clinical trial. The objectives of this trial are to:

Determine the effectiveness of the SURE: CRC4D multi-component implementation strategies to increase CRC screening uptake among patients with diabetes.Evaluate the fidelity, feasibility, and acceptability of SURE: CRC4D implementation.Refine the SURE: CRC4D toolkit based on multi-level user feedback and conduct an evaluation to promote scalability and sustainable use.

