### Methods

#### Study participants and setting

This single arm trial will be conducted in six FQHC clinical sites in New Jersey. Eligibility criteria for the FQHC clinics include: (1) provide care to at least 450 patients aged 50–74 years; (2) 10% of patient population previously diagnosed with diabetes; (3) located in New Jersey; and, 3) clinical and administrative leadership willing to engage in the intervention and research requirements (interviews, data validation, process evaluation). Implementation outcomes will be assessed using mixed methods guided by the EPIS constructs (see Table 2). The methods of this study have been reported using Standard Protocol Items: Recommendation for Interventional Trials (SPIRIT) guidelines (Supplemental file 1).

During the implementation a clinic-based registry of patients eligible for CRC screening will be developed for each clinic at baseline and updated at six and 12 months post-baseline. Patient eligibility criteria will include: (1) patients not up-to-date or due for CRC screening [4]. based on electronic health record (EHR) documentation (e.g. FOBT/FIT test in last year, flexible sigmoidoscopy within 4 years, or colonoscopy within 9 years), (2) previous diagnosis of type II diabetes, (3) age-eligible for CRC screening (45–74 years of age) and (4) ) FIT/FOBT that has been ordered for more than 6 months that has not been completed or a sigmoidoscopy or colonoscopy referral that has not been completed for 12 or more months. Patients are excluded if they have EHR documentation medical conditions not concordant with standard CRC screening intervals (e.g. prior CRC diagnosis, inflammatory bowel disease, renal failure, etc.) [4].

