### Patient level: clinical effectiveness outcome and implementation assessment

The primary outcome variables to assess clinical effectiveness will be the clinic level proportion of patients with diabetes who: (a) receive any CRC screening and (b) complete a colonoscopy at 12 months from baseline. An exploratory analysis will assess clinic-level CRC screening completion by glucose control (controlled vs. uncontrolled, i.e., HbA1c > 9 at 12 months). Patient level data is collected in aggregate and will include no identified personal health information.

Patient acceptability will be assessed through the assessment of patient rates of opting-out and non-adherence of CRC screening. This rate will be based on the proportion of CRC screening among patients with diabetes compared to overall eligible patient population (without diabetes) in each clinic.

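### The 25% and 15% success rules measure absolute 12-month screening of unscreened patients with no usual-care rate to subtract, so they cannot show an increase

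*Protocol article*

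**What the plan says.** The stated objective (Methods and design, list of trial objectives) is comparative: "Determine the effectiveness of the SURE: CRC4D multi-component implementation strategies to increase CRC screening uptake among patients with diabetes". The evaluation section repeats it as a question about whether CRC screening rates rise.

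The design has no control group: "This single arm trial will be conducted in six FQHC clinical sites in New Jersey". Patients enter the clinic registry because the health record shows them as not up to date or due (Study participants and setting).

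The Quantitative analysis section sets two decision rules. For any test: "We will declare our intervention a success if at least 25% of those unscreened are screened at 12-month follow-up". For the optimization claim: "We will declare the optimization of screening a success if 15% of those unscreened are screened with a colonoscopy or flexible sigmoidoscopy at 12-months". The intervals are judged against a fixed figure: "The confidence intervals will be compared to 25" percent. The support offered is "Overall improvement metrics are comparable to improvements in previous CRC screening implementation studies in FQHCs". The section has average screening rates calculated at baseline and at 12 months, each with an interval, but specifies no difference between them. The article gives no usual-care conversion rate, meaning the share of unscreened patients who would be screened within 12 months without the intervention.

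Patients without diabetes appear once as a comparison, and only to define patient acceptability: "This rate will be based on the proportion of CRC screening among patients with diabetes compared to overall eligible patient population (without diabetes").

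**The concern.** The objective asks about a change, while the rule answers with a level. In a group chosen for being unscreened, the proportion screened can hardly do anything but rise over a year. Every screen counts towards the 25%, including those the clinic would have delivered anyway. The near-zero starting value comes from selection and says nothing about what a year of usual care would have produced.

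Two errors become possible. A clinic group with brisk background screening could be declared a success with no intervention effect. A group with low background screening and a real gain could miss the bar. If exactly 25% is observed, the part due to the strategies is 15 points when usual care delivers 10%, 5 points when it delivers 20%, and nothing when it delivers 25%. The article says the results will help refine the toolkit for a definitive cluster randomized trial, so this difference matters for what follows.

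**Working it through.** **The plan's own figure.** Power calculations assumes 50 patients with diabetes per clinic and 40% up to date. That gives 50 × (1 − 0.40) = 30 unscreened per clinic and 6 × 30 = 180 overall, so the stated 30 reproduces. No null rate, power or intraclass correlation is stated, so there is no power figure to reproduce.

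**How large could usual-care conversion be?** The article does not say, so I used an illustrative steady state. Inputs from the article are 40% up to date (Power calculations), and one year of cover from a stool test and ten from colonoscopy (Table 1). Assumed inputs are the share of up-to-date patients covered by stool tests and their screening behaviour.

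*Model A: everyone who is due has the same chance of screening.* With stool-test share f, screens per year are S = 0.40 × [f + 0.1(1 − f)]. Patients who lapse during the year are due for half of it on average, so conversion of the unscreened is S / (0.60 + 0.5S).

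| f | S | Conversion |
|---|---|---|
| 0 | 0.040 | 6.5% |
| 0.25 | 0.130 | 19.5% |
| 0.37 | 0.173 | 25.2% |
| 0.50 | 0.220 | 31.0% |

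*Model B: stool testers repeat yearly with probability a.* To keep 40% up to date, conversion is u = [0.40 − 0.36(1 − s) − 0.40·s·a] / 0.60, with s the stool-test share.

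| s | a | u |
|---|---|---|
| 0 | any | 6.7% |
| 0.37 | 0.6 | 14.1% |
| 0.37 | 0.4 | 19.0% |
| 0.37 | 0.2 | 23.9% |
| 0.50 | 0.4 | 23.3% |
| 0.50 | 0.2 | 30.0% |
| 0.75 | 0.4 | 31.7% |
| 1 | 0.8 | 13.3% |

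More extreme inputs go higher, but these suffice: the clinic-wide rate can stay flat at 40% while conversion of the unscreened lies on either side of 25%.

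**Chance of passing the 25% rule with no intervention effect.** This is the probability of at least 45 of 180 (0.25 × 180 = 45). The first column is exact binomial with independent patients. The second is a beta-binomial simulation at an assumed intraclass correlation of 0.05.

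| Usual-care rate | Independent | ICC 0.05 |
|---|---|---|
| 15% | <0.1% | 1.6% |
| 20% | 6.0% | 15.5% |
| 25% | 52.9% | 51% |
| 30% | 94.1% | 84% |

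**The 15% rule.** In Model A, conversion by colonoscopy is 0.04(1 − f) / (0.60 + 0.5S): 6.5% at f = 0, 4.5% at f = 0.25 and 2.8% at f = 0.50. If every up-to-date patient had instead had sigmoidoscopy (five-year interval), it is 0.08 / (0.60 + 0.04) = 12.5%. That is an extreme, since the Background says sigmoidoscopy is not widely used. All lie below 15%. The chance of at least 27 of 180 is about 0.004% at 6.5% and 2.2% at 10%; at the 12.5% extreme it is about 18%.

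**The case against.** **The design is modest and says so.** The article describes a single arm, calls its estimates preliminary and leaves the definitive test to a cluster randomized trial. This stands, and it lowers the severity. It does not remove the point, because the article still states an effectiveness objective and a declaration of success.

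**The registry may be hard to convert.** Eligibility criterion (4) requires an uncompleted stool test order or referral. If it applies jointly with the other criteria, the pool consists of known non-completers and usual-care conversion is probably lower than either model gives. Equal chance of screening in Model A probably also overstates the background. Both stand: the documents show that the background rate is unknown, not that it is high.

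**The interval may decide.** If success required the lower limit of an 80% t-interval across six clinics to exceed 25%, false success would be 7–8% at a 25% usual-care rate, though still 23–40% at 30% (assumed ICC 0.02–0.10). The text does not say whether the point estimate or the interval governs.

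**The baseline may not be zero.** The abstract, the outcome definition and Power calculations also allow a denominator of all patients with diabetes, about 40% of them up to date at baseline. On that reading a before-after contrast is collected that already reflects usual care. A reader might infer that every planned baseline is 0% by construction. That goes too far: near zero holds for the registry, and some patients listed as due may still be inside the Table 1 intervals. But the success rule is written for the unscreened and does not use the clinic-wide contrast.

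**The justification may fit.** A reader might infer that the 25% misuses changes reported in earlier studies as a level. Whether the cited studies report changes or conversion rates cannot be checked here, so I do not rest on it.

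**Conclusion.** The concern holds in limited form. The rules compare an absolute conversion rate with a fixed number, have no usual-care rate behind them, and so cannot by themselves answer whether screening increased. For the 25% rule, background screening could plausibly fall on either side of the bar. The risk of a false success is negligible if usual care converts 15% or fewer (independent patients) and large at 25% or above.

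Two stronger readings are tempting. One is that usual care would pass the 25% rule; the documents give no rate that shows this, and the steady-state figures rest on assumed stool-test shares and behaviour. The other is that both rules are equally exposed; under the same model usual-care conversion stays below 15%, so what is shown there is an overstated effect, not a false success.

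Severity: should be fixed, given the single-arm, preliminary design.

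**What to change.** At the baseline health-record pull, have each clinic run the same aggregate query dated 12 months earlier: patients with type II diabetes meeting the registry criteria on that date, and how many were screened in the following 12 months, by any test and by colonoscopy or sigmoidoscopy. Make the effectiveness estimate the clinic-level difference, post-year conversion minus pre-year conversion, with its interval. Describe 25% and 15% as feasibility benchmarks, not as evidence of effectiveness. If the back-dated query is not possible, make the relabelling alone. Optionally, add the contrast with eligible patients without diabetes as a sensitivity analysis.

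Costs:
- One further aggregate query per clinic. Past order and referral status must be reconstructed across different record systems, which is real work.
- A wider interval. At 25%, the 80% half-width is 1.2816 × √(0.25 × 0.75 / 180) = 4.1 points for a single rate and 1.2816 × √(2 × 0.25 × 0.75 / 180) = 5.8 points for a difference of two independent rates, before clustering.
- Secular trend remains possible in a before-after difference. Spillover to patients without diabetes would pull the optional contrast towards no effect.

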**Methods:**

Guided by the Exploration, Preparation, Implementation and Sustainment Framework, we conducted a stakeholder-engaged process to identify multi-level change objectives for implementing optimized CRC screening for patients with diabetes in FQHCs. To identify change objectives, an implementation planning group of stakeholders from FQHCs, safety-net screening programs, and policy implementers were assembled and met over a 7-month period. Depth interviews (*n* = 18–20) with key implementation actors were conducted to identify and refine the materials, methods and strategies needed to support an implementation plan across different FQHC contexts. The planning group endorsed the following multi-component implementation strategies: identifying clinic champions, development/distribution of patient educational materials, developing and implementing quality monitoring systems, and convening clinical meetings. To support clinic champions during the initial implementation phase, two learning collaboratives and bi-weekly virtual facilitation will be provided. In single group, hybrid type 2 effectiveness-implementation trial, we will implement and evaluate these strategies in a in six safety net clinics (*n* = 30 patients with diabetes per site). The primary clinical outcomes are: (1) clinic-level colonoscopy uptake and (2) overall CRC screening rates for patients with diabetes assessed at baseline and 12-months post-implementation. Implementation outcomes include provider and staff fidelity to the implementation plan, patient acceptability, and feasibility will be assessed at baseline and 12-months post-implementation.

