**Assessments**												
EHR abstraction	x											x
Clinic Staff and Clinician Qualitative Interviews	x	x	x			x						x
Practice Information Form	x					x						x
Clinic Staff and Clinician Questionnaires	x					x						x

The implementation will be rolled out over a 12-week period. Initially, clinics will be asked to identify 1–3 clinic champions, with at least one clinician (i.e., physician, advanced practice nurse, physician assistant) per team. Each team will meet with the external practice change facilitator approximately two weeks prior to the initial learning collaborative. This initial facilitation meeting is introductory, with the goal of encouraging clinic champions to reflect about the current clinic CRC screening strategies and diabetes care management processes prior to the 1st virtual learning collaborative. Clinical champions will attend the 1- hour virtual learning collaborative, where the materials in the SURE: CRC4D toolkit will be provided and reviewed, and each clinic team will formulate practice change goals. Teams will decide on how to deploy the toolkit strategies at their FQHC sites over the course of the next ten weeks. The practice facilitator will support the clinic champion team in the development, implementation, and refinement of the local practice change plan. The champions will meet with the practice facilitator every two weeks for 8 weeks (4 times). During this time, the plan will be refined and adjusted based on feedback from clinic leaders and practice staff members and identified strengths and barriers that are encountered during the implementation effort. At week 10, a second learning collaborative will be virtually convened, providing a forum where the different clinic teams can share their successes and obstacles during the development and execution of their plan. This forum will foster cross-team learning and idea generation that can inform the refinement of the SURE: CRC4D toolkit and sustainability of practice change efforts. Two weeks after the second learning collaborative, a final virtual facilitation meeting will be held to reflect and refine the practice plan to support sustainability.

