### Evaluation of the effectiveness and implementation of SURE: CRC4D

The effectiveness and implementation of SURE: CRC4D will be evaluated using a mixed method learning evaluation strategy, where ongoing data collection and analysis are used to refine implementation to optimize adoption of CRC screening for patients with diabetes [52, 53]. This evaluation is designed to address two research questions: (1) are the adapted implementation strategies clinically effective in increasing CRC screening rates for patients with diabetes; and, (2) are the implementation strategies feasible and acceptable to implementers (e.g., clinicians and staff) and patients in FQHCs? This evaluation builds an evidence base about the effectiveness of the implementation strategies in a real-world context and allows for the collection of data that can be used to refine the implementation toolkit for a larger scale, definitive cluster randomized controlled trial. Guided by EPIS, contextual factors were selected based on suggestions from clinical stakeholders, community partners, and previous literature suggesting they may influence implementation success [54–56] (see Table 4). The following assessments and measures will be collected to evaluate the trial:

**Table 4 Tab4:** Study measures

	Baseline & 12-month post implementation

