**Effectiveness: Clinic Level Patient Outcomes***	
Demographics	QUANT
Glycemic Control (HgbA1C < 9)	QUANT
Any CRC screening/patients eligible	QUANT
Colonoscopy completion/patients eligible	QUANT
CRC rate by glycemic control	QUANT

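### The 15% success rule for the colonoscopy outcome also counts flexible sigmoidoscopy, so it can be met with patients who do not meet the declared primary outcome

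*Protocol article*

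**What the plan says.** The second primary outcome is colonoscopy alone wherever it is declared:

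- The abstract (Methods) lists the primary clinical outcomes as "1) clinic-level colonoscopy uptake and (2) overall CRC screening rates for patients with diabetes assessed at baseline and 12-months post-implementation".
- Table 4 lists the measure as "Colonoscopy completion/patients eligible".
- The section on the patient-level clinical effectiveness outcome defines the two primary variables as the clinic-level proportions of patients with diabetes who "receive any CRC screening and (b) complete a colonoscopy at 12 months from baseline".

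The section Quantitative analysis then sets two success rules. One is a 25% bar for any screening among those unscreened. The other concerns the optimization of screening: "We will declare the optimization of screening a success if 15% of those unscreened are screened with a colonoscopy or flexible sigmoidoscopy". No other success rule for the colonoscopy outcome appears in the article.

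On timing, the outcome section counts 12 months from baseline. The abstract and the column header of Table 4 ("Baseline & 12-month post implementation") count from implementation.

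**The concern.** A success rule should be applied to the outcome that it judges. Here a patient who has a sigmoidoscopy and no colonoscopy fails primary outcome (b) but counts towards the 15% rule that decides whether (b) succeeded.

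The article does not treat the two procedures as interchangeable. Its Background gives mortality reductions of 68% for colonoscopy and 28% for sigmoidoscopy, and Table 1 gives intervals of 10 and 5 years. The stated rationale is to give priority to colonoscopy because of its longer interval. No reason is given for admitting sigmoidoscopy at the point of decision.

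The trial has a single arm, so the fixed bars carry the success decision. The error also runs one way: a wider numerator can never make the bar harder to reach. Patient data are collected only in aggregate. If a clinic returns one combined count, the colonoscopy-only figure may not be recoverable later.

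**Working it through.** **Step 1. The planned denominator.** Power calculations assumes 50 patients with diabetes per clinic, of whom 40% are up to date. This gives 50 × (1 − 0.40) = 30 per clinic, which reproduces the stated target. Six clinics give 6 × 30 = 180.

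**Step 2. The bar as a count.** 0.15 × 180 = 27 patients.

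**Step 3. Which rules are affected.**

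| Rule (Quantitative analysis) | Declared outcome | Same procedures? |
|---|---|---|
| 25%, any screening | (a) any CRC screening | Yes |
| 15%, colonoscopy or sigmoidoscopy | (b) colonoscopy | No |

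**Step 4. Illustrative size.** Let c be the true proportion with a colonoscopy and s the further proportion with a sigmoidoscopy only. The chance of meeting the bar is P(X ≥ 27), with X binomial on n = 180. The success probability is c under the declared outcome and c + s under the rule as written. The article gives neither c nor s, so both are assumptions:

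| c | s = 0 (colonoscopy alone) | s = 1% | s = 2% | s = 3% |
|---|---|---|---|---|
| 10% | 0.02 | 0.06 | 0.13 | 0.24 |
| 12% | 0.13 | 0.24 | 0.38 | 0.53 |
| 13% | 0.24 | 0.38 | 0.53 | 0.67 |
| 15% | 0.53 | 0.67 | 0.79 | 0.88 |

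At c = 13%, an extra 2% takes the chance from 0.24 to 0.53. At s = 0 the two definitions coincide. The calculation reads the rule as an observed proportion of at least 15% and ignores clustering by clinic, because no intraclass correlation is stated.

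**Step 5. The time point.** The places that fix the clock are:

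- Study participants and setting updates the registry at 12 months post-baseline.
- Table 3 marks EHR abstraction at months 1 and 12, so baseline and the start of implementation share month 1.
- Process data outcomes starts the later interviews at 6 months post implementation, and Table 3 marks them at month 6.
- Clinic staff measures gives the second questionnaire at 12 months post-implementation, and Table 3 marks it at month 12.

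The article thus uses months post-implementation for months counted from the start of implementation. On that usage the two wordings describe the same date.

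**The case against.** The strongest reply is that the effect has no documented size and may be close to nil. The Background says that sigmoidoscopy is little used in the United States, and with no sigmoidoscopies the rule and the outcome agree. This stands as a limit on the size, but the contradiction in the text remains.

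A second reply is that the 15% bar was written for the combined measure, so narrowing the numerator at the same bar tightens the criterion. Relabelling the rule as a direct-visualisation criterion, separate from the primary outcome, would also make the text consistent. Both points are fair. But relabelling would leave primary outcome (b) with no success rule, and colonoscopy alone is the definition in all three places where the outcome is declared.

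A third reply is that the study is sized only for preliminary estimates with an 80% confidence interval, ahead of a larger trial. That lowers the stakes. The article nevertheless declares success by these rules.

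A reader might infer two stronger points, and the document supports neither:

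- **That both success rules depart from the declared outcomes.** The 25% rule covers the same procedures as outcome (a). Quantitative analysis also names no starting point for its 12 months that conflicts with the outcome section.
- **That follow-up runs to about month 15.** The article says that "The implementation will be rolled out over a 12-week period", and one could add 12 months to the end of that period. But nothing is scheduled after month 12, and the 6- and 12-month assessments sit at months 6 and 12 of Table 3. What remains is loose wording.

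**Conclusion.** The point holds for the 15% optimization rule only. As written, the rule counts patients whom primary outcome (b) excludes, and it can only be easier to meet than a rule on the declared outcome.

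The size cannot be established from the article. The change from 0.24 to 0.53 is an illustration resting on an assumed 13% colonoscopy rate, an assumed further 2% with sigmoidoscopy, exactly 180 patients and no clustering. Given the article's own remark on sigmoidoscopy use, the practical effect is probably small. It would decide the result only when the colonoscopy rate falls just short of 15%.

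This should be corrected before data are extracted, because it concerns a decision rule and costs almost nothing to put right. The difference between 12 months from baseline and 12 months post-implementation is a minor matter of wording, and no change in the screening rates should be attributed to it.

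**What to change.** - In Quantitative analysis, apply the 15% rule to colonoscopy completion, as declared in the abstract, Table 4 and the outcome section. Report colonoscopy or sigmoidoscopy combined as a secondary measure.
- Have each clinic return two separate counts at extraction: patients with a colonoscopy, and patients with a sigmoidoscopy but no colonoscopy. Either measure can then be rebuilt from the aggregates.
- Use one phrase for the time point throughout, 12 months from baseline, and align the abstract and the Table 4 header and note with the outcome section and Table 3.

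The cost is a few sentences and one extra count per clinic. The sample size stays at 30 per clinic. The downside is a slightly stricter criterion, since the 15% figure was written for the wider numerator. The team should confirm before extraction that it still intends 15% for colonoscopy alone.
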